Donor chimerism, as determined by short tandem repeat testing in multiplex battery with 1-5% sensitivity, was not seen in most patients. Only two patients developed donor chimerism and both patients died; one patient clearly died of GVHD and the other possibly from GVHD. Hence, we were able to document complete responses, some of which were durable, with cell infusions in the absence of demonstrable engraftment.

Evaluation of serum cytokine levels during the haploimmunostorm revealed elevations of multiple cytokines including interferon γ which in the murine model has been shown to play a role in the host versus tumor response [16,17]. The pattern of cytokine elevations was distinct from the patterns seen with the engraftment syndrome and GVHD. These elevations were felt to be related to the haploimmunostorm manifestations.

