### Toxicities/Safety

Patients will be monitored for cell infusion syndrome and cytokine release syndrome. Patients will be given methylprednisolone for Grade 3 or 4 Toxicities based on NCI CTC version 4.0 criteria. Furthermore, percent chimerism will be assessed using short tandem repeats 2 days post cellular infusion, 14 post cellular infusion, and every 14 days thereafter as long as chimerism persists (Figure 1). Lack of chimerism will obviate the risk of GVHD. After 6 patients have been followed for a minimum of 2 months after cellular infusion, the Brown University Oncology Research Group (BrUOG) will review safety data prior to reopening accrual. Data from the safety review will be shared with the FDA.

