**Figure 1 F1:**
[figure not shown]
Schematic depicting key time points for blood sample accrual for translational studies to be incorporated into the Cellular Therapy Protocol (HLA= Human leukocyte antigen, KIR= Killer-cell immunoglobulin-like receptor, STR= short tandem repeat, CRS= Cyokine release syndrome).

Adverse events will be scored according to the NCI CTCAE version 4 criteria. Dose limiting toxicity (DLT) will be defined as any of the following treatment related events:

• Grade 3 graft versus host disease lasting > 7 days

• Grade 4 graft versus host disease of any duration

• Grade 3 infusion related symptoms lasting > 7 days

• Grade 4 infusion related symptoms of any duration

In the safety run-in for the first 6 patients, if 2 or less of 6 patients have a dose limiting toxicity then accrual will be allowed to extend to a total of 25 patients. If 3 or more of 6 patients have a DLT, or there is one grade 5 treatment-related adverse events, protocol accrual will be suspended. If this circumstance occurs, the BrUOG data safety monitoring group will review the adverse event data and make appropriate recommendations to the BrUOG scientific advisory board and the FDA about the study.

The safety evaluation of all 25 evaluable patients is a major objective of this study. A 35% rate of treatment-related adverse events from cellular infusion will be considered unacceptable.

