### Statistical considerations

As noted above, the safety of cellular therapy administration in the first six patients will be reviewed by the FDA and the BrUOG Data Safety Monitoring Board (DSMB). These reviews will be shared with our institutional IRB. If the treatment appears safe, as determined by the FDA and the BrUOG DSMB with institutional IRB agreement, the protocol may be reopened to treat a total of 25 patients. A sample size of 25 patients will differentiate between a 10% level of activity and a 30% level of activity. Specifically, the hypothesis to be tested is:

H_0:_ p< 0.1 versus H_1_: p> 0.3

A Simon two-stage design will be used in this study. The first 15 evaluable patients will be assessed for activity. The trial will be terminated early if activity is observed in 0 or 1 of these 15 patients, and it will be concluded that the true activity rate is unlikely to be > 10%. If activity is demonstrated in at least 2 patients, accrual will continue until a total of 25 evaluable patients are enrolled. If activity is observed in 5 or fewer of 25 patients, the null hypothesis will be accepted and it will be concluded that there is not sufficient activity to merit further investigation of the regimen. Otherwise, it will be concluded that the treatment regimen has sufficient activity to warrant further investigation.

The characteristics of this study design are as follows:

This design yields a type I error rate of <0.05 (α=0.03) and power of 80% when the true response rate is 30%.

Overall survival, time to progression, and progression free survival will be determined by the Kaplan Meier method (from the time of study enrollment).

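### The 35% toxicity limit has no defined event, count or action attached, and the only DLT count rule stops at patient 6

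*Protocol article*

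**What the plan says.** The relevant text is in the Toxicities/Safety section of the protocol article, after the Figure 1 legend, and in Statistical considerations.

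- **Run-in pass rule.** For the first six patients, "if 2 or less of 6 patients have a dose limiting toxicity then accrual will be allowed to extend" to 25 in total.
- **Suspension rule.** "If 3 or more of 6 patients have a DLT, or there is one grade 5 treatment-related adverse events, protocol accrual will be suspended".
- **Event counted.** "Dose limiting toxicity (DLT) will be defined as any of the following treatment related events": grade 3 graft-versus-host disease (GVHD) or infusion symptoms lasting more than 7 days, or grade 4 of either.
- **Overall safety.** "The safety evaluation of all 25 evaluable patients is a major objective of this study", followed by: "A 35% rate of treatment-related adverse events from cellular infusion will be considered unacceptable". No grade, count, time of assessment or consequence is given.
- **Review after the run-in.** "After 6 patients have been followed for a minimum of 2 months after cellular infusion", the research group reviews safety before accrual reopens. Statistical considerations adds: "If the treatment appears safe, as determined by the FDA and the BrUOG DSMB with institutional IRB agreement, the protocol may be reopened".
- **Later looks.** The only later interim look is after 15 evaluable patients, in the Simon two-stage design. It counts activity, not toxicity.

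**The concern.** The section sets a safety limit and a safety rule that do not connect. The limit is 35% of an ungraded event class. The rule counts a narrower class, DLTs, in six patients only. Two DLTs in six (33%) is a pass just below the limit, and six patients cannot reliably tell a rate near 35% from a tolerable one. Once accrual reopens, 19 of the 25 patients are treated with no stated DLT count that would prompt a pause, although safety in all 25 is called a major objective.

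The background gives a reason for care. In the earlier haploidentical study two patients developed donor chimerism and both died: "one patient clearly died of GVHD and the other possibly from GVHD". This trial drops the irradiation and G-CSF used there (Study rationale), so the earlier safety experience does not carry over directly in either direction.

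**Working it through.** **1. The plan's own design figure.** The article gives no operating characteristic for the safety rule. Its only design figures are for efficacy (stop at 0 or 1 of 15; accept the null at 5 or fewer of 25). With X1 ~ Bin(15, p) and X2 ~ Bin(10, p),

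P(reject) = Σ(x = 2 to 15) P(X1 = x) · P(X2 ≥ 6 − x).

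This gives 0.0328 at p = 0.10 and 0.8017 at p = 0.30, which agrees with the stated 0.03 and 80%. The efficacy design is sound.

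**2. The run-in count.** Inputs: n = 6, pass at 2 or fewer DLTs. For a true DLT rate p,

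P(pass) = (1−p)^6 + 6p(1−p)^5 + 15p²(1−p)^4.

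At p = 0.35: 0.0754 + 0.2437 + 0.3280 = 0.647.

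| True DLT rate | P(count does not suspend) |
|---|---|
| 15% | 0.953 |
| 20% | 0.901 |
| 25% | 0.831 |
| 35% | 0.647 |
| 50% | 0.344 |

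These figures ignore the grade 5 trigger. If the 35% included fatal events in 2%, 5% or 10% of patients (assumed values), the chance that neither trigger fires would be Σ(x = 0 to 2) C(6,x)(0.35−q)^x(0.65)^(6−x) = 0.597, 0.525 or 0.417.

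**3. After the run-in.** At a 35% DLT rate the expected number of further DLTs in patients 7 to 25 is 19 × 0.35 = 6.65. If the trial stops for inactivity at 15 patients, it is 9 × 0.35 = 3.15.

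**4. An illustrative cumulative boundary.** Suspend and review at ≥3/6, ≥4/10, ≥6/15 or ≥7/20 DLTs. The probability of crossing is found by carrying forward the distribution of counts that have not yet crossed. At 35%, the first crossing at patient 10 has probability

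0.0754 × P(4 of 4) + 0.2437 × P(≥3 of 4) + 0.3280 × P(≥2 of 4) = 0.0754 × 0.0150 + 0.2437 × 0.1265 + 0.3280 × 0.4370 = 0.175.

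The cumulative figure is therefore 0.353 + 0.175 = 0.528. Continuing gives 0.588 at 15 patients and 0.687 at 20.

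| True DLT rate | P(suspend), run-in count only | P(suspend), with boundary |
|---|---|---|
| 15% | 0.047 | 0.082 |
| 20% | 0.099 | 0.190 |
| 25% | 0.169 | 0.344 |
| 35% | 0.353 | 0.687 |
| 50% | 0.656 | 0.961 |

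**5. Scope of the grade 5 trigger.** Assume a 15% DLT rate and an independent 2% treatment-related death rate.

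- Run-in count, grade 5 trigger limited to six patients: 1 − 0.9527 × 0.98^6 = 1 − 0.9527 × 0.8858 = 0.156.
- Run-in count, grade 5 trigger over all 25: 1 − 0.9527 × 0.98^25 = 1 − 0.9527 × 0.6035 = 0.425.
- Boundary, grade 5 trigger over all 25: 1 − 0.9183 × 0.6035 = 0.446.

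The unresolved wording alone moves the chance of a pause from 0.16 to 0.43, assuming all 25 patients are treated.

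**The case against.** Three stronger conclusions are tempting, and the document does not support them.

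**That there is no death rule after patient 6.** The limit of six patients is attached to the DLT half of the suspension sentence. The grade 5 half has no such limit of its own. It stands in the run-in paragraph, so a run-in-only reading is possible, but so is a trial-wide one. What stands is an ambiguity, not an absence.

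**That the run-in clears an unacceptable regimen two times in three.** The 35% applies to treatment-related adverse events, not DLTs, so 0.647 rests on equating the two. Nor does a passing count clear the regimen. Reopening also needs two months of follow-up and FDA and safety board judgement with IRB agreement, and the Discussion allows the protocol to be altered at that point. So 0.647 is only the chance that the DLT count does not suspend accrual. The mismatch of events does not rescue the limit, however. DLTs are the narrower class, so a 35% adverse event rate implies a DLT rate no higher than 35%, and a pass probability of 0.65 or more. Read without a grade, the 35% might be exceeded by expected reactions alone, because the earlier study describes fever as a universal feature of its post-infusion syndrome.

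**That the 35% is checked only once all 25 patients have been treated.** The text gives no time for the assessment, so this is an inference.

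Two further objections carry weight. The earlier deaths followed irradiation and G-CSF mobilisation and occurred in the only two patients with donor chimerism, so they give no reliable death rate for this trial. And a journal article condenses a fuller protocol, which may contain continuing monitoring. The point therefore rests on what the article does state: a numerical limit and a count rule that do not meet. The regulatory and board review, while real, is described once, after patient 6, and supplies no criterion for the other 19 patients.

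**Conclusion.** The point holds in a limited form. The 35% limit has no defined event, count, look or action, and the only stated DLT count rule ends at patient 6. Taking the 35% as a DLT rate, with independent patients and the grade 5 trigger set aside, the run-in count fails to suspend accrual with probability 0.65. About 6.7 further DLTs would then be expected in patients 7 to 25 if all are treated, with no stated DLT rule to prompt a pause. Whether a treatment-related death after patient 6 suspends accrual cannot be settled from the text. The 0.65 depends on the assumed reading of the 35%; the missing link between limit and rule does not.

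**What to change.** 1. Define the event to which the 35% applies, including its grade, and reconcile it with the DLT definition. State when it is assessed and what follows if it is exceeded.
2. Add a cumulative DLT suspend-and-review boundary for patients 7 to 25, derived from that limit, with values set by the safety board. The boundary in the working is an illustration only. It raises P(suspend) at a 35% DLT rate from 0.35 to 0.69.
3. State whether the grade 5 suspend-and-review trigger covers all 25 patients or the run-in only.

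The text change is about a paragraph, and the DLT data are already to be scored. The real cost is more review pauses at rates that may be tolerable: from the DLT boundary alone, 0.05 to 0.08 at 15%, 0.10 to 0.19 at 20% and 0.17 to 0.34 at 25%. If the grade 5 trigger is now run-in only and is extended as well, the two changes together move the figure from 0.16 to 0.45 at a 15% DLT rate and an assumed independent 2% death rate. These are pauses for review, not terminations. Because the illustration keeps the six-patient rule, the 0.65 run-in pass rate is unchanged; the gain is all in patients 7 to 25.

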#### Infusion of HLA haploidentical pheresed cells

In order to increase the number of patients eligible for cellular infusion, we next evaluated the infusion of haploidentical peripheral blood cells into 26 patients with refractory hematologic malignancies [15]. Granuloctye colony stimulating factor (G-CSF) mobilization was used for collection of peripheral blood cells. Following 100 cGy of total body irradiation (TBI), patients were infused with escalating levels of CD3+ cells. The study recruited thirteen patients with AML, six with NHL, five with MM, one with ALL and one with chronic myeloid leukemia (CML). No responses were seen in the eight patients treated with 1 × 10^6^ or 1 × 10^7^ CD3+ cells per kg. At higher CD3+ dose levels of 1–2 × 10^8^ per kg, objective responses were seen in 14 out of 18 patients. Two of six patients with NHL remained free of disease at 76 months and 82 months, respectively, while two additional NHL patients obtained partial responses (PR). There were 3 durable CR lasting 8, 11 and 31 months, respectively, and 7 transient responses in 13 patients with AML (Table 1). Remarkable, all responses occurred outside of donor chimerism. Serial bone marrow biopsies performed in several patients showed evidence of large tumor reduction and early resumption of normal hematopoiesis.

**Table 1 T1:** **Summary of responses seen in 26 patients with refractory hematological malignancies treated with haploidentical PBSC infusions [**[15]**]**

**Malignancy**	**Complete response**	**Partial response**	**Transient response**	**Total response**
AML	3/13 (23%)	0/13 (0%)	7/13 (54%)	10/13 (77%)
NHL	2/6 (33%)	2/6 (33%)	0/6 (0%)	4/6 (66%)

Toxicities included well-tolerated myelotoxicity. An immediate post-infusion immunologic syndrome, which we termed “haploimmunostorm”, was observed. This was universally characterized by fever and variably by skin rash, diarrhea, liver dysfunction, effusions, respiratory distress and edema. These signs and symptoms were variable between patients. It only occurred in patients infused with at least 1 × 10^8^ CD3+ cells per kg, began 14 hours after cell infusion, and remitted rapidly with methylprednisolone, 2 mg/kg/day within 6–8 hours of the onset of the haploimmunostorm. Typically, we allowed this syndrome to persist for at least 48 hours as it was hypothesized that this might be a component of the therapeutic response.

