### Primary and secondary objectives

The primary objective is to assess the overall response rate of cellular immune therapy with HLA-haploidentical peripheral blood pheresed cells in patients with relapsed/refractory hematological malignancies.

Secondary objectives will more accurately describe the clinical effect by assessing the time-to-progression, PFS and OS for patients with relapsed/refractory hematologic malignances following HLA-haploidentical cellular therapy. An additional secondary objective is to evaluate the rate of dose-limiting toxicities of HLA-haploidentical peripheral blood pheresed cellular infusions.

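### The 35% unacceptable-toxicity benchmark counts related events of any grade, so the expected febrile cytokine release syndrome alone would very probably reach it, and it does not match the DLT objective

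*Protocol article*

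**What the plan says.** All the safety rules are in the Toxicities/Safety section of the protocol article.

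- **Grading:** "Adverse events will be scored according to the NCI CTCAE version 4 criteria".
- **DLT:** "Dose limiting toxicity (DLT) will be defined as any of the following treatment related events". The list has four entries: graft-versus-host disease or infusion-related symptoms, each at grade 3 for more than 7 days or at grade 4 for any duration.
- **Run-in:** "if 2 or less of 6 patients have a dose limiting toxicity then accrual will be allowed to extend to a total of 25 patients". Three or more DLTs in six patients, or one treatment-related grade 5 event, suspends accrual.
- **Full cohort:** "The safety evaluation of all 25 evaluable patients is a major objective of this study", followed directly by "A 35% rate of treatment-related adverse events from cellular infusion will be considered unacceptable".

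Under Primary and secondary objectives, the safety objective is to "evaluate the rate of dose-limiting toxicities".

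The section on infusion of HLA haploidentical cells describes the syndrome seen after infusion in the pilot: "This was universally characterized by fever and variably by skin rash, diarrhea, liver dysfunction, effusions, respiratory distress and edema". On dose it says: "It only occurred in patients infused with at least 1 × 10^8^ CD3+ cells per kg". It adds that the syndrome was usually left to run for at least 48 hours because it might contribute to the response. The Study rationale attributes the CRS to the patients at 1–2 × 10^8 CD3+ cells per kg in general terms. Study design sets that same dose range for this trial.

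**The concern.** The benchmark sentence names the widest safety event available: any adverse event related to the infusion, at any grade. The article itself leads one to expect such events often, since a febrile reaction is the anticipated and possibly desired effect of the treatment. A limit on that event measures mainly whether the intended reaction took place, and says little about whether it was tolerable.

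The sentence also departs from the rest of the safety plan. The run-in lets accrual continue with DLTs in 2 of 6 patients (33%). The final benchmark then calls 35% unacceptable for an event that includes mild, self-limiting fever. Followed literally, it could condemn a regimen that produced no DLT. If the team sets it aside as unworkable, the full cohort has no working benchmark beyond the estimated DLT rate.

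**Working it through.** **1. The plan's own figures.** The only operating characteristics given are for efficacy (Statistical considerations): 15 patients then 25, stop at 1 or fewer responses, fail at 5 or fewer. Summing P(x₁ of 15) × P(at least 6 − x₁ of the next 10) over x₁ ≥ 2 gives a type I error of 0.0328 at a 10% response rate and a power of 0.8017 at 30%. The stated 0.03 and 80% are reproduced. The 35% safety limit has no stated derivation or operating characteristic.

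**2. The limit as a count.** 0.35 × 25 = 8.75. Since 8/25 = 32% and 9/25 = 36%, an observed proportion of at least 35% means 9 or more patients. The article does not say whether 35% is an observed or a true rate, so this reading is an assumption.

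**3. Chance of reaching it.** Let p be the share of patients with at least one related event of any grade, here febrile CRS and nothing worse, independent between patients:

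P(X ≥ 9) = Σ from x = 9 to 25 of C(25, x) pˣ (1 − p)²⁵⁻ˣ

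The article gives no value for p, so a range is shown.

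| Assumed p | P(at least 9 of 25) |
|---|---|
| 35% | 0.53 |
| 40% | 0.73 |
| 50% | 0.946 |
| 60% | 0.996 |
| 70% | 0.9999 |

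The chance is 95% at p of about 50%. None of these cases includes a DLT.

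**4. The same cut-off on a narrow event.** If the 9-of-25 limit applied to an event such as the DLT, the chance of reaching it would be 0.0005 at a true rate of 10%, 0.047 at 20% and 0.53 at 35%. The cut-off can therefore discriminate; the event it is attached to prevents it.

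**5. Against the run-in.** The chance of at most 2 DLTs in 6 is 0.90 at a true DLT rate of 20% and 0.65 at 35%. The run-in thus often passes a regimen with a 35% DLT rate, while the final sentence rejects 35% for events of any severity.

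**The case against.** The strongest objection is that the CRS incidence is unknown. In the pilot, fever was universal among patients who had the syndrome, and no count of those patients is given. A minimum dose below which it did not occur shows that the dose is necessary, not that it is sufficient. Pilot patients also received 100 cGy of total body irradiation and G-CSF-mobilised cells, and this trial uses neither. All of this stands. A reader might infer that the benchmark must be breached whatever the true safety, and the document does not support that: at 35% incidence the chance is only 0.53. It does not rescue the benchmark, however. The Study rationale describes CRS as general at this dose and omits conditioning in order to strengthen the host response, and about 50% incidence already gives a 95% chance of a breach.

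A second objection is that the sentence carries no stopping action and that other safeguards exist. That also stands. A reader might infer that the trial cannot meet its safety objective, but the DLT rate can be estimated whatever becomes of this sentence, and the run-in rule and its review operate independently.

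A third objection is that 35% lies close to the tolerated 33% and follows the DLT definition, so DLTs were probably meant. That is plausible, and the full protocol may be clearer, but the printed sentence says something else.

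A reader might also infer from the word evaluable that infused patients could drop out of the safety denominator. The article does not say that the word means evaluable for response in this sentence, and population definitions are commonly left to fuller documents. No point is made of it.

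**Conclusion.** The point holds in a limited form. As written, the full-cohort benchmark counts related events of any grade, including a syndrome that the article anticipates and may welcome. It also disagrees with the DLT-rate objective and with the DLT-based run-in. At plausible CRS rates it would very probably be reached without any severe toxicity: 0.73 at 40% incidence, rising to 0.996 at 60%. It then gives no information about safety.

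This rests on three assumptions: an incidence range that the document does not supply, the reading of the limit as 9 or more of 25 patients, and the expectation that CRS will occur without irradiation or G-CSF much as it did with them. The fault lies in a threshold that is stated but attached to the wrong kind of event. It does not depend on detail left to an unseen document, and it is confined to this one benchmark.

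**What to change.** Reconcile the 35% sentence with the DLT definition, the grade 5 rule and the DLT-rate objective by tying it to a defined severe-event endpoint. The sponsor must choose that endpoint. The protocol's own DLT is the natural candidate because the objective already names it. Substituting the DLT list as printed would not be enough: it covers only graft-versus-host disease and infusion-related symptoms and does not list grade 5, so treatment-related deaths must be expressly counted. The sponsor should also decide how other severe related events are handled.

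State whether 35% refers to the observed or the true rate, and report the chosen rate with an exact 95% confidence interval against 35%.

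The cost is a short protocol amendment and the sponsor's decision on the endpoint. No extra patients are needed. If the endpoint is built from graded, treatment-related events, the planned CTCAE scoring already supplies the data.
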